## Outcomes

Postoperative sequelae after surgical removal of the impacted mandibular third molar will be estimated by assessing pain, facial swelling, and mouth opening.

Pain: The visual analog scale (VAS)
^
9
^ will be used to assess pain on a scale ranging from 0 to 10. The worst imaginable pain will be graded as 10, and the absence of pain will be graded as 0.

Facial swelling will be measured using a metric tape and standard reference points.
^
7
^ The following reference points will be used for the measurement:
•Soft tissue pogonion - Tragus•The angle of the mandible - Corner of the eye•Corner of mouth - Tragus

Mouth opening: The maximum interincisal distance will be recorded using a metric scale with standardized ruler and a digital Vernier caliper.
^
10
^

Salivary Prostaglandin E2 and serum C-reactive protein levels will be measured by ELISA (enzyme-linked immunosorbent assay (ELISA) preoperatively (T0) on the second postoperative day (T1) and fifth postoperative day (T2).

Patient satisfaction regarding therapy: Study subjects will classify their experience from 1 to 5, where 1 = poor, 2 = fair, 3 = good, 4 = very good, and 5 = excellent.

The need for rescue analgesics will be evaluated by counting the number of tramadol capsules or tablets required by the patient until the fifth postoperative day (T2).

### Participant timeline

Pain, facial swelling, mouth opening, serum C-reactive protein, and salivary prostaglandin E2 levels will be recorded preoperatively (T0) on the second postoperative day (T1) and fifth postoperative day (T2).

Patient satisfaction regarding therapy and the need for rescue analgesics will be recorded on the fifth postoperative day.

### Sample size

The study will be a non-inferiority trial with a continuous outcome.

The sample size was established based on data obtained from a previous study conducted by Salgia et al.
^
11
^ Serum C-reactive protein level was chosen as the primary outcome variable.

Formula using mean difference

$$n1=n2=2\frac{{\left(Z_{\alpha }+Z_{\beta }\right)}^{2}\sigma^{2}}{{\left(\delta \right)}^{2}}$$

$$Z_{\alpha }=1.96\;$$

α = Type I error at 5% at both sides two tailed

Z
_β_ = 0.84 = Power at 80%

Primary Variable = CRP (C-reactive protein) levels

The mean difference after treatment CRP (mean ± SD) for the diclofenac group was 16.305 ± 3.977 (as per the reference article).
^
10
^

Considering 20% clinically relevant margin for aescin = (

16.305∗20)/100=3.26

Sample size:

$$N=n1=n2=2\frac{{\left(1.96+0.84\right)}^{2}{\left(3.977\right)}^{2}}{{\left(3.261\right)}^{2}}=23$$

Assuming 10% dropout = 2

Total sample size required = 23 + 2 = 25 each group.

Thus, a total sample size of 50 subjects presenting with impacted mandibular third molars will be enrolled in the study.

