## Objectives

The objectives of the present study are as follows:
1.To compare the efficacy of aescin and diclofenac sodium in managing postoperative sequelae following surgical removal of impacted mandibular third molars.2.To compare the efficacy of aescin and diclofenac sodium in manipulating salivary Prostaglandin E2 (PGE2) and serum C-reactive protein (CRP) levels in patients undergoing surgical removal of the impacted mandibular third molar.3.To assess patient satisfaction regarding therapy.4.To evaluate the need for rescue analgesics in the postoperative period.

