Graziani et al. (2017) enrolled 40 patients in a case-control study demonstrating systemic inflammation following third molar removal. Patients who underwent third molar removal had more significant systemic inflammation, oxidative stress, and triglyceride levels than controls, and the first postoperative week had increased WBC counts and serum C-reactive protein and fibrinogen levels. The baseline values of the markers were observed three months after extraction. Higher systemic inflammation is associated with impacted third molars, and their elimination may signify a novel method for investigating acute inflammation and defining favorable systemic outcomes in humans.
^
8
^

Mehra et al. (2013) conducted a double-blind, randomized clinical trial of 80 patients to assess the effect of four different pharmacological regimens on prostaglandin E2 (PGE2) levels in urine and saliva. Saliva and urine samples were collected at planned intervals. After removing the impacted lower third molars, the findings were compared with clinical progression. Patients who received ibuprofen fared significantly better in terms of most parameters. They further concluded that PGE2 is measurable in saliva and urine, and its rise and fall can be detected in both saliva and urine. They further suggested that PGE2 correlates with subjective and objective clinical symptomatology and that administration of anti-inflammatory drugs manipulates its levels in the body.
^
5
^

The current scientific literature must be more extensive in demonstrating the correlation of the drug’s efficacy with reliable inflammation markers and associated clinical symptomatology.

Considering this, the present study will be a randomized, double-blind, non-inferiority trial to compare the efficacy of aescin and diclofenac sodium in the management of postoperative pain, swelling, and mouth opening, as well as their effects on salivary Prostaglandin E2 and serum C-reactive protein levels after surgical removal of the impacted mandibular third molar. The trial will be conducted as per SPIRIT guidelines.
^
15
^

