In conclusion, the proposed study is expected to positively manipulate the levels of salivary Prostaglandin E2 and serum C–reactive protein, which are reliable inflammatory markers. The study may show clinically acceptable responses in the management of postoperative pain, swelling and mouth opening with administration of aescin. The outcome of this study may provide an efficacious and safe alternative to conventional nonsteroidal anti-inflammatory drugs for managing postoperative discomfort following third molar surgery.

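### Non-inferiority is sized on serum CRP alone, so the trial cannot confirm the anticipated claim about postoperative discomfort from a CRP result or a non-significant test on symptoms

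*Protocol article*

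**What the plan says.** All places are in the Protocol article.

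- **Sample size.** The design is declared: "The study will be a non-inferiority trial with a continuous outcome". The endpoint is named: "Serum C-reactive protein level was chosen as the primary outcome variable". The inputs are CRP inputs: the value "for the diclofenac group was 16.305 ± 3.977 (as per the reference article", a margin of 20% of that mean (3.26), "Type I error at 5% at both sides two tailed" and 80% power. The result is 23 per group, raised to 25 for dropout, 50 in total.
- **Objectives.** The first is "To compare the efficacy of aescin and diclofenac sodium in managing postoperative sequelae"; the marker objective comes second. The Outcomes section says the sequelae are assessed by pain, facial swelling and mouth opening. CRP is listed there as a separate measurement.
- **Statistical analysis plan.** VAS, facial swelling, mouth opening, PGE2 and CRP appear together under the primary-variable label. Outcome variables are compared between the two groups with an unpaired t-test.
- **Discussion, closing paragraphs.** The trial is described as a non-inferiority comparison in the management of pain, swelling and mouth opening, as well as of effects on PGE2 and CRP. The last paragraph hopes for an "alternative to conventional nonsteroidal anti-inflammatory drugs for managing postoperative discomfort following third molar surgery". The Conclusion of the Abstract says much the same.

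**The concern.** The non-inferiority question has a margin on one scale only, serum CRP. The claim that clinicians would act on concerns what patients experience after surgery, and no margin is set for that. Two separate routes could lead to an unsupported statement.

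1. CRP meets its margin and is read as showing comparable control of symptoms. That needs evidence linking the two, and the article does not supply it. The symptom correlation it reports from a cited trial is for the other marker: "PGE2 correlates with subjective and objective clinical symptomatology". The article presents CRP as a sensitive indicator of inflammation and healing. It also makes the correlation of CRP with symptoms one of this trial's own aims, and the Discussion says the literature on such correlations is still too thin. The link is thus treated as a question to be studied. The article also describes aescin as venotonic, antiedematous, glucocorticoid-like and acting on the bradykinin pathway, so its CRP and pain effects need not track those of an NSAID.
2. A t-test on VAS, swelling or mouth opening is non-significant and is read as showing no loss of efficacy. Without a margin, that result is uninformative about non-inferiority.

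At stake is a recommendation on postoperative treatment that rests on no confirmatory comparison of symptoms.

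**Working it through.** **1. Reproduce the plan's own figure.**
Inputs (Sample size section): mean 16.305, SD 3.977, margin 20%, z-values 1.96 and 0.84.
- Margin = 0.20 × 16.305 = 3.261.
- n per group = 2 × (1.96 + 0.84)² × 3.977² / 3.261² = 23.3, stated as 23 (24 if rounded up).
- Power at 23 per group = Φ(3.261 / (3.977 × √(2/23)) − 1.96) = Φ(0.82) = 79.4%; at 25 per group it is 82.6%.

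The figure reproduces to within rounding, from CRP inputs alone. The problem is not arithmetic.

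**2. What 23 per arm can support on any other continuous endpoint.**
For 80% power, one-sided 2.5% and a true difference of zero, the smallest margin is (1.96 + 0.8416) × √(2/n) SDs.
- n = 23: 2.8016 × 0.2949 = 0.83 SD.
- n = 25: 2.8016 × 0.2828 = 0.79 SD.

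**3. Precision of a between-group difference.**
Half-width of the 95% interval = t(0.975, 44) × SD × √(2/23) = 2.015 × 0.2949 × SD = 0.59 SD.

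The article gives no SD for this trial's VAS. For assumed SDs:

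| Assumed VAS SD | 95% half-width, 23 per arm |
|---|---|
| 1.5 | ±0.89 |
| 2.0 | ±1.19 |

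**4. Power on VAS for assumed margins.**
Power = Φ(margin / (SD × √(2/23)) − 1.96). Both the SD and the margin are assumptions, because the article gives neither.

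| Assumed margin (VAS points) | SD 1.5 | SD 2.0 |
|---|---|---|
| 1.0 | 62% | 40% |
| 1.5 | 92% | 72% |
| 2.0 | >99% | 92% |

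So 23 per arm may or may not be enough for pain. The answer depends on quantities that have not been fixed.

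**5. The sections side by side.**

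| Section | Role of CRP | Role of pain, swelling, mouth opening |
|---|---|---|
| Sample size | Sole primary outcome, with margin, SD and power | None stated |
| Objectives | Second objective | First objective |
| Statistical analysis plan | One of five under the primary-variable label | Three of the five, compared by t-test |
| Discussion | Covered by the non-inferiority description | Covered by the non-inferiority description |

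Only the first row carries a margin.

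**The case against.** **The discomfort statements are hedged and are not a decision rule.** This stands. The Abstract and Discussion speak of what is expected or may be shown, and they cover PGE2 and CRP too. A reader might infer that the plan will declare aescin an alternative for discomfort once CRP meets its margin. No section says that, and the point does not rest on it.

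**Symptoms are measured directly.** This also stands. VAS, swelling, mouth opening, tramadol count and satisfaction are all recorded, so the trial is not silent on discomfort. But measurement followed by a t-test does not give a non-inferiority conclusion.

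**The article does offer some support for CRP.** In the cited 90-patient comparison with mefenamic acid, diclofenac had both the lower VAS and the lower CRP. In the cited A-PRF study, a faster fall in CRP went with fewer symptoms of regional inflammation. These are group results moving the same way. They do not show that a CRP difference within 3.26 means comparable symptoms, and neither study included aescin.

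**The trial might be called too small for pain.** A reader might compare the half-widths with the VAS difference of 3.46 − 2.58 = 0.88 in the 90-patient study and conclude that a worthwhile loss could never be excluded. The documents do not support that.
- The 0.88 is an observed difference between two drugs, not a margin.
- At an assumed SD of 1.5 the half-width exceeds it by only 0.01 with 23 per arm (0.891), and falls below it with 25 (0.853).
- Large SDs sit badly with that study: 0.88 at p < 0.05, with an assumed 45 per group and an unpaired t-test, implies an SD below about 0.88 / (1.987 × √(2/45)) = 2.1.

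**Sizing on a single primary outcome is common practice.** True, and CRP may be kept. The confirmatory claim should then be limited to it.

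**Conclusion.** The point holds as a mismatch between the endpoint that carries the non-inferiority design and the claim the article anticipates. CRP alone has a margin, SD and power, yet the Discussion describes non-inferiority for pain, swelling and mouth opening, and the Statistical analysis plan section ranks those measures equally with CRP. This part rests on the text alone.

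The size is best stated without an assumed SD: with 23 per arm, 80% non-inferiority power needs a margin of about 0.83 SD or more on any continuous endpoint, and the 95% half-width is about 0.59 SD. The VAS figures (±0.89 to ±1.19) rest on assumed SDs of 1.5 to 2 and illustrate the scale only. They do not show that the sample is inadequate for pain. The trial remains usable for its CRP question.

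**What to change.** 1. Reconcile the Statistical analysis plan section with the Sample size section, so that CRP is the single primary outcome in both.
2. In the Abstract conclusion and the closing paragraphs of the Discussion, limit the confirmatory non-inferiority conclusion to serum CRP.
3. List VAS, swelling, mouth opening and rescue use as secondary outcomes, each reported as a between-group difference with a 95% interval.
4. State that no claim of equivalence, or of an alternative for managing discomfort, will be drawn from a CRP result or from a non-significant t-test on a clinical measure.

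This changes wording only. The sample size, visits and measurements stay as they are. The cost is a narrower claim. If the sponsor wants a confirmatory statement on symptoms, one clinical outcome would have to become primary, with its own justified margin and SD, and the trial would have to be re-sized.

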Singh et al. (2021) conducted a study on 90 patients that aimed to compare the efficacy of diclofenac sodium and mefenamic acid in managing pain after mandibular impacted third molar surgery and to assess changes in C-reactive protein (CRP) levels as an inflammation marker. The study involved surgical removal using standardized procedures, with patients divided into two groups: one receiving diclofenac sodium (50 mg) and the other mefenamic acid (500 mg) for three days. Pain was evaluated using the visual analog scale (VAS), revealing a mean VAS of 2.58 for diclofenac and 3.46 for mefenamic acid (p < 0.05). Postoperative CRP levels increased significantly in both groups. However, diclofenac showed lower CRP levels compared to mefenamic acid. The findings suggested that diclofenac sodium is effective for pain relief and that CRP evaluation can serve as a useful indicator of postoperative inflammation.
^
14
^

Nowak et al. (2021) conducted a study of 60 patients to assess the impact of A-PRF application during third molar surgery and its effect on C-reactive protein concentrations and wound healing. Patients who received A-PRF after the procedure had a faster rate of decreased CRP levels. They also suggested that A-PRF application significantly reduced the symptoms of regional inflammation and incidence of dry socket.
^
6
^

In a detailed review of escin, Gallelli (2019) suggested that it has potent anti-inflammatory, antiedematous, venotonic, and endothelial protective properties. They described the basic mechanism of action of escin. Oral escin and its topical gel have been demonstrated to increase venous tone and reduce edema, resulting in quantifiable clinical progress in patients with blunt injury and chronic venous insufficiency.
^
4
^

Isola et al. (2018) conducted a clinical trial of eighty-two patients needing mandibular third molar extraction surgery. The study participants were randomly allocated into three groups. Group 1, placebo; Group 2, ibuprofen; Group 3, a phytotherapeutic drug (baicalin 190 mg, bromelain 50 mg, and escin 30 mg). All medications were prescribed twice daily for five days after tooth extraction. A visual analog scale was used to assess pain. A metric scale was used to record alterations in facial contours and mouth opening in millimeters. The outcome of this clinical trial implies that phytotherapeutic drug therapy effectively manages postoperative pain and discomfort.
^
9
^

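### The non-inferiority margin of 3.26 is 20% of a one-arm diclofenac CRP figure and is not tied to diclofenac's effect over no treatment, so meeting it would not by itself establish efficacy

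*Protocol article*

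**What the plan says.** All statements are in the protocol article.

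- **Design and primary variable (Sample size):** "The study will be a non-inferiority trial with a continuous outcome", and "Serum C-reactive protein level was chosen as the primary outcome variable".
- **Error rates (Sample size):** "α = Type I error at 5% at both sides two tailed", with a Z of 1.96, and "0.84 = Power at 80"%.
- **Source of the margin (Sample size):** "The mean difference after treatment CRP (mean ± SD) for the diclofenac group was 16.305 ± 3.977", taken from a cited study. The margin follows as "Considering 20% clinically relevant margin for aescin", which is 3.26. No other reason for 20% is given.
- **Arms (Trial design; Interventions: description):** diclofenac and aescin only, with no placebo or untreated arm.
- **CRP after this surgery (Discussion):** in a cited comparison of diclofenac and mefenamic acid, "Postoperative CRP levels increased significantly in both groups". The next sentence adds that CRP was lower on diclofenac than on mefenamic acid.
- **Intended conclusion (Abstract, Conclusion; last paragraph of the Discussion):** the result "may provide an efficacious and safe alternative to conventional nonsteroidal anti-inflammatory drugs" for postoperative discomfort. The paragraph before that last one again calls the trial a non-inferiority trial.

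**The concern.** A trial without a placebo arm can use non-inferiority to argue that the new drug works only if the margin is smaller than the effect of the control drug over no treatment. If the margin is as large as that effect or larger, a drug that does nothing can meet it.

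The margin here is a percentage of a figure observed in one arm. The label attached to 16.305 does not settle whether it is a change from baseline or a level after treatment. On either reading it mixes the response to the operation with whatever diclofenac contributes. The article's own account of CRP rising after surgery in two NSAID groups shows that a one-arm figure does not isolate a drug effect. Twenty percent of it therefore says nothing about how much of diclofenac's benefit would be retained.

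What is at stake is the step from mean CRP being close on the two drugs to aescin being an efficacious alternative.

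**Working it through.** **Inputs from the Sample size section.** Reference figure 16.305, SD 3.977, margin 20%, Z values 1.96 and 0.84, 23 evaluable per group, 25 enrolled per group, 10% dropout.

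**Input that the article does not give.** E, the effect of diclofenac on CRP against placebo or no treatment, in the units of the 16.305. It is an assumption and is varied below.

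**Step 1: reproduce the plan's figures.**
Margin = 0.20 × 16.305 = 3.261.
n per group = 2 × (1.96 + 0.84)² × 3.977² / 3.261² = 2 × 7.84 × 15.817 / 10.634 = 23.3.
The plan states 23; rounding up gives 24. The sample-size arithmetic is not the issue here.

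**Step 2: the chance that an inactive drug passes.** If aescin had no effect on CRP, its true mean would be worse than diclofenac's by E. Non-inferiority is declared when the upper limit of the two-sided 95% confidence interval for the difference lies below 3.261, which is a one-sided 2.5% test. With 10% dropout, 45 of the 50 patients are evaluable (22 and 23):

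SE = 3.977 × √(1/22 + 1/23) = 1.186, with 43 degrees of freedom.

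The test statistic then follows a noncentral t distribution with noncentrality (3.261 − E) / SE. The critical value is 2.017.

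| Assumed E | E as share of 16.305 | (3.261 − E) / 1.186 | Chance that an inactive drug passes |
|---|---|---|---|
| 0 | 0% | 2.75 | 77% |
| 0.82 | 5% | 2.06 | 52% |
| 1.63 | 10% | 1.37 | 27% |
| 2.45 | 15% | 0.69 | 10% |
| 3.26 | 20% | 0 | 2.5% |
| 4.08 | 25% | −0.69 | 0.4% |
| 4.89 | 30% | −1.37 | 0.05% |
| 6.52 | 40% | −2.75 | about 0 |

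With 23 per group and a normal approximation, SE = 3.977 × √(2/23) = 1.173. The chance is then 79% at E = 0 and still 2.5% at E = 3.26, so the picture does not depend on the method.

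**Step 3: what the margin retains.** The margin equals the whole effect at E = 3.26. It leaves half of the effect only if E is at least 2 × 3.261 = 6.52.

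**Step 4: what a margin tied to the effect would cost.** As an illustration only, take a margin of half of E, with SD 3.977, one-sided 2.5% and 80% power. This needs 249 per group at E = 2, 94 at E = 3.26, 63 at E = 4 and 24 at E = 6.52, where the margin is again the planned 3.261. Without a value for E no single corrected sample size can be given.

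**The case against.** **The risk is conditional.** It exceeds 2.5% only if E is below 3.26 and vanishes soon above that; the 77% is the case in which diclofenac itself does nothing to CRP. This stands. Nothing in the article makes the low end of the range more likely than the high end. A reader might infer that an inactive drug is likely to be declared non-inferior; the article supports only that this has not been excluded.

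**16.305 may not be a plain CRP level.** This also stands. A reader might take the margin to be 20% of a raw CRP value, but the article labels the figure a mean difference after treatment and does not say whether it is a change or a level. The point holds on both readings, because neither is a difference against no treatment.

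**CRP may respond to the drug.** The cited comparison found lower CRP on diclofenac than on mefenamic acid, which suggests that CRP responds to treatment, and a rise after surgery does not show that the drug effect is small. Both remarks are fair. But a difference between two active drugs does not give E.

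**The efficacy sentence is cautious and does not rest on CRP alone.** The article says the outcome may provide an alternative, and it also plans pain, swelling, mouth opening, PGE2, rescue use and satisfaction. This is why the point is confined to what the CRP margin alone can support.

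**A fixed absolute margin is ordinary practice.** Agreed. That 3.26 might be a different percentage of this trial's own diclofenac mean is no defect.

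**The test is assumed, and the article is condensed.** The Statistical analysis plan section names t-tests and ANOVA, not a margin test, so the probabilities presuppose one in line with the stated 1.96. Historical evidence on diclofenac could exist in a fuller document. But the rule for the margin is written out completely here, and it uses a quantity that cannot carry the efficacy argument. That makes it a badly fixed rule and not an omitted detail.

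**Conclusion.** The point holds in a limited form. The margin of 3.26 is not linked to diclofenac's CRP effect over placebo or no treatment, so meeting it would show that mean CRP is similar on the two drugs and would not by itself establish that aescin is efficacious.

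The size depends wholly on the unknown E. The chance that an inactive drug passes ranges from 77% at E = 0, through 27% at 1.6 and 10% at 2.4, to the nominal 2.5% at 3.26 and below 0.5% from 4.1 upward. These figures assume SD 3.977, 45 evaluable patients and a one-sided 2.5% margin test. The documents do not support the claim that the margin actually exceeds diclofenac's effect, only that they do not show it to be smaller.

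**What to change.** 1. In the Sample size section, and in the Discussion paragraph that calls this a non-inferiority trial, state that meeting the margin supports only this: mean CRP on aescin is less than 3.26 worse than on diclofenac.
2. In the Abstract conclusion and the closing paragraph of the Discussion, do not rest the claim of an efficacious alternative for postoperative discomfort on that result.
3. Alternatively, cite an estimate of diclofenac's CRP effect over placebo or no treatment and show that 3.26 is a stated fraction of it. If the cited effect calls for a smaller margin, recompute the sample size.
4. In either case, say whether 16.305 is a change or a level.

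Items 1, 2 and 4 are wording. Their cost is a narrower headline claim. Item 3 could raise the sample size if the cited effect is small, as the illustration above shows. The Study status section places the trial at the pilot stage, so either route still looks feasible.

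### Rounding down twice leaves 25 per group slightly short of the stated 80% power once 10% drop out

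*Protocol article*

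**What the plan says.** All inputs are in the Sample size section of the protocol article.

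- Design: "The study will be a non-inferiority trial with a continuous outcome", with serum CRP as the primary variable.
- Error rate: "α = Type I error at 5% at both sides two tailed", entered as Z = 1.96.
- Power: "0.84 = Power at 80" percent.
- Standard deviation: "The mean difference after treatment CRP (mean ± SD) for the diclofenac group was 16.305 ± 3.977 (as per the reference article").
- Margin: "Considering 20% clinically relevant margin for aescin", taken as 20% of 16.305 and entered in the formula as 3.261.

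The section prints the two-sample normal-approximation formula with these values and gives the result as 23 per group. It then states "Assuming 10% dropout = 2" and "Total sample size required = 23 + 2 = 25 each group". It ends: "Thus, a total sample size of 50 subjects presenting with impacted mandibular third molars will be enrolled in the study".

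The Statistical analysis plan section names the unpaired t-test for comparing the two groups.

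**The concern.** The section can be checked against itself. A sample size from a power formula is a minimum, so a fractional result is rounded up. Here both fractional results, the base size and the dropout allowance, were rounded down. Applying the stated dropout rate to the stated enrolment should leave at least the stated evaluable number, and it does not.

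This calculation is the only justification given for enrolling 50 patients, and it concerns the primary variable of a non-inferiority trial. In such a trial lower power means a higher chance of an inconclusive result when aescin is truly no worse. The 80% figure is also likely to be repeated when the trial is reported, although the planned numbers do not quite deliver it.

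**Working it through.** **Inputs (Sample size section).** SD 3.977; margin 0.20 × 16.305 = 3.261; Z values 1.96 and 0.84; dropout 10%; 25 enrolled per group. A two-sided 5% level with Z = 1.96 is the same as one-sided 2.5% for a non-inferiority comparison. The true difference is taken as zero, as the formula implies.

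**Step 1: the protocol's own figure.**

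n = 2 × (1.96 + 0.84)² × 3.977² / 3.261² = 2 × 7.84 × 15.817 / 10.634 = 23.32.

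The protocol prints 23, so the figure is reproduced apart from the rounding. Rounded up, it is 24.

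**Step 2: the dropout allowance.** 10% of 23 is 2.3, printed as 2. Two losses out of 25 are 2/25 = 8%, not 10%. At 10% loss, 25 × 0.9 = 22.5 per group remain, or 45 in total. This is below 23 as well as below 24.

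**Step 3: power at the numbers that remain.**

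- Normal approximation: power = Φ(3.261 / (3.977 × √(2/n)) − 1.96). At n = 22.5 the first term is 2.750, so power = Φ(0.790) = 78.5%.
- Unpaired t-test: noncentral t, one-sided 2.5%, with the same margin and SD. For 45 patients split 22 and 23, power is 76.7%.

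| Evaluable per group | Normal approximation | Unpaired t-test |
|---|---|---|
| 22 | 77.6% | 75.7% |
| 22.5 (22 and 23 for the t-test) | 78.5% | 76.7% |
| 23 | 79.4% | 77.6% |
| 24 | 81.1% | 79.4% |
| 25 | 82.6% | 81.1% |

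The first whole number to reach 80% is 24 by the protocol's formula and 25 by the t-test. The protocol has 25 enrolled, not 25 evaluable.

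**Step 4: size with every step rounded up.**

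- Normal approximation: 24 / 0.9 = 26.7, so 27 per group (54 in total).
- Unpaired t-test: 25 / 0.9 = 27.8, so 28 per group (56 in total).

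**Step 5: does the form of the dropout adjustment matter?** Adding 10% to 24 gives 26.4 and dividing 24 by 0.9 gives 26.7; both round up to 27. From 23 the results are 25.3 and 25.6; both round up to 26. Once rounding is upward, the two methods give the same size.

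**The case against.** The strongest reply is that the gap is trivial. By the protocol's own formula it is 1.5 percentage points (80 − 78.5). If only one patient per group is lost, 24 remain and power is 81.1%; with no loss it is 82.6%. An SD of about 3.91 instead of 3.977, which is 1.8% lower, would restore 80% at 22.5 per group, and an SD taken from one earlier study is not known that precisely. All of this stands. It limits the weight of the point but does not make the printed figures right.

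A second reply is that sizing by the normal approximation is a common and openly stated convention, so the t-test figure reflects a change of method and not an error in the protocol's sums. This also stands. The two power figures should be reported side by side, and a target size from one method should not be paired with a power from the other.

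Three stronger readings are tempting and are not supported:

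- A reader might infer that adding the allowance, instead of dividing by 0.9, is a separate cause. Step 5 shows that it changes nothing once rounding is upward.
- A reader might infer that the trial is seriously underpowered. On the stated inputs the shortfall is 1.5 to about 3 points.
- A reader might expect a baseline-adjusted analysis to make up the loss. That depends on the correlation between baseline and postoperative CRP, which the document does not give. The SD is described as that of a mean difference after treatment and may already be the SD of a change, so no gain can be assumed.

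**Conclusion.** The point holds as a small error in a stated figure. On the protocol's own inputs and its own 10% dropout, 50 enrolled patients leave about 45 evaluable. Power is then about 78.5% by the protocol's formula or about 77% by the unpaired t-test, not 80%. The cause is mainly that 23.32 became 23 and 2.3 became 2.

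The result assumes the stated SD of 3.977 and margin of 3.261, a one-sided 2.5% level, no true difference between the drugs, dropout spread evenly over the groups, and no contribution to the comparison from patients who drop out. It takes the SD and the margin as given and does not assess whether they are well chosen.

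**What to change.** Keep 50 patients and correct the Sample size section to say, in substance: the formula gives 23.3, rounded up to 24 evaluable per group by the normal approximation (25 for the t-test); with 50 enrolled and 10% dropout, about 45 are expected to be evaluable, giving power of about 78.5% (normal approximation) or 77% (unpaired t-test).

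This costs one restated passage and a slightly less favourable power figure. Recruitment, treatment and analysis are unchanged. If the sponsor prefers to hold 80% by the protocol's own formula after 10% loss, the size is 27 per group, which means four more patients in total (54 instead of 50).
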